The Hispanic/Latino population in the United States is a racial/ethnic group that may benefit from novel treatment focused on improving psychological well-being [12]. There are 57 million [13] Hispanic/Latino people in the United States, and they represent the second fastest growing ethnic/racial minority group [14,15]. Hispanic/Latino people exhibit a disproportionately higher burden of cardiovascular disease risk factors [3,16]. In addition, the Hispanic/Latino population has a higher incidence rate for CVD-related comorbidities (eg, chronic kidney disease) when compared with non-Hispanic populations, with 30% mortality attributable to CVD and its sequelae [14,17,18]. Additional research is needed, however, to explore strategies that boost psychological well-being specifically in Hispanic/Latino adults and whether this leads to better heart health and BP management. To date, pilot trials highlight that Hispanic/Latino adults find interventions targeting psychological well-being both enjoyable and beneficial [19,20].

Observational evidence links psychological well-being with better overall health, more healthy coping tendencies, improved quality of life, and healthy longevity [8,21]. Psychological well-being focuses on positive thoughts and feelings at the individual level, which may be key in promoting healthy behaviors in hypertension management [8]. Evidence suggests that psychological well-being is related to healthier BP profiles and plays a protective role in disease incidence [7,22]. In over 1000 healthy non-Hispanic adults, a large prospective study found that higher levels of psychological well-being were associated with a decreased likelihood of incident hypertension at a one-year follow-up [23]. In 126 British civil servants, aggregate baseline levels of happiness were negatively associated with 3-year measures of systolic BP, independent of known confounders.

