After determining full eligibility, participants will be enrolled in the trial by providing written informed consent. After completing baseline assessments, participants will be randomly assigned in a 1:1 ratio to the intervention or active control condition using block randomization alternating between varying block sizes of 4, 6, or 8. The principal investigator created a random allocation table using Sealed Envelope, after which it was uploaded to REDCap to define the randomization model of *¡Alégrate!* to ensure proper blocking and stratification by sex (male and female) and use of antihypertensive medication (yes and no). A trained research staff generated allocation assignment through REDCap. It should be noted that REDCap conceals the allocation table and associated sequencing from research staff to prevent selection bias. Finally, given the pilot nature of a Phase II trial, blinding occurs only at the level of data analysis.

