#### Antecedent Variables and Qualitative Data

In addition to the main outcomes of interest, we will also collect variables hypothesized to be antecedents or important confounders when exploring intervention effects. The list of antecedents or covariates is summarized in Table 2 and includes the following: (1) demographic factors, (2) anthropometric measurements, (3) acculturation, (4) level of religiosity, (5) self-reported mental and physical health, and (6) current or previous history of medical comorbidities. In addition, we will conduct qualitative exit interviews to capture facilitators and barriers in using the tablet computer to access *¡Alégrate!* curricular content. Indeed, qualitative process evaluation techniques further inform metrics of acceptability and utility for the modality of content distribution. Finally, we will also analyze data describing the overall use of the website by trial participants, including the number of website logins per participant, average length of screen time per site visit, and extent to which enrollees completed and recorded practicing of at-home exercises.

**Table 2 table2:** Outcome, mediator, and intervention-based measures.

Measure					Description

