### Planned Analyses

The primary outcome of the *¡Alégrate!* trial focused on prospective changes in B*P* values, that is, both sitting BP and 24-hour ambulatory readings. The first aim was to examine the efficacy of the intervention in reducing B*P* values immediately postintervention (ie, 5 weeks) and at the 12-week follow-up period, that is, Exams 2 and 3. The second aim was to explore whether the intervention leads to significant improvements in psychological well-being and greater adherence to healthy behavioral practices. We will additionally test whether psychological well-being and healthy behaviors serve as mediators when exploring intervention effects on BP control. The third aim is to test intervention effects on circulating markers of inflammation, specifically high-sensitivity C-reactive protein.

Descriptive statistics, at baseline, will summarize participant characteristics for the full sample and stratified by intervention arm. Bivariate tests will be conducted to compare the intervention and control conditions to ensure compatibility across key variables (eg, demographic factors, well-being profiles, etc) and to test the success of the randomization protocol. Discrepancies in baseline values across conditions will inform covariates for inclusion when testing our main hypotheses of interest. In addition, we will document the number of missing observations over time to assess the potential for bias resulting from significant dropout and differential attrition by condition. We will perform independent sample two-tailed *t* tests and/or Fisher exact tests to compare baseline characteristics of enrollees who completed the trial versus those who prematurely dropped out, allowing us to test possible predictors of attrition.

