#### Aim 2: To Test Intervention Effects on Psychological Well-Being and Adherence to Healthy Behaviors and to Subsequently Explore Whether Improvements in Psychological Well-Being and Adherence to Healthy Behaviors Are Responsible for Better BP Control, That Is, Mediation Testing

Similar analytic techniques will be implemented for Aim 2 as used for Aim 1. The interaction of Group×Time will test if greater improvements are evident for psychological well-being and engagement in healthy behaviors (eg, dietary intake and self-reported physical activity) at 5 weeks postbaseline for the treatment arm as compared with the active control group. RM-ANOVA will also be used to examine whether the *¡Alégrate!* intervention is associated with greater improvements in psychological well-being and engagement in healthy behavior. In addition to reporting nominal *P* values, we will document the number of tests conducted and associated Bonferroni correction. Finally, we will conduct mediation analysis to test whether psychological well-being and healthy behaviors serve as intermediates (or mediators) through which *¡Alégrate!* impacts BP control. Tests of mediation will follow the recommendations of Shrout and Bolder to bootstrap product terms using Mplus. Given the dependency of indirect effects on the time interval, for multiwave models, we will compute overall, rather than time-specific, indirect effects.

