### Strengths and Limitations

Limitations are evident in the design and eventual deployment of the *¡Alégrate!* web-based trial. Selective enrollment has the potential to introduce bias as Hispanic/Latino people with limited technological proficiency may decline to participate in the trial, or if enrolled, may have difficulty in connecting to Wi-Fi or in navigating the study site. Future trials may want to explore more user-friendly modalities that require little to no coaching that may be more appealing to less technologically savvy community members. We are recruiting in a Chicago-based neighborhood with a large population of Hispanic/Latino adults, the majority of which are of Mexican ancestry. Thus, the findings of the trial may not generalize to the wider, more heterogeneous Hispanic/Latino population across the United States with differences by country of origin, nativity status, and level of acculturation. Our design includes an active control condition where participants are asked to report their emotions, thrice weekly, via our web-based platform. This may not adequately adjust for effects derived from social support and contact with research staff as imparted in the treatment group. Future trials may want to deploy a more active control condition where participants’ access to web-based content is unrelated to the outcome of interest, for example, money management skills. Finally, blinding occurs only at the level of data analysis, and both trial participants and assessors (research staff collecting outcome data) are aware of randomization assignment, which can introduce unintended bias.

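### The Aim 2 mediation test fixes no adjustment for the non-randomised mediator-to-BP path, so a non-causal correlation between well-being and BP can be read as mediation

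*Protocol article*

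**What the plan says.** The heading of Aim 2 in the Protocol article sets the question: "Explore Whether Improvements in Psychological Well-Being and Adherence to Healthy Behaviors Are Responsible for Better BP Control". The method follows in the same section: "Tests of mediation will follow the recommendations of Shrout and Bolder to bootstrap product terms using Mplus". For multiwave models the section chooses overall over time-specific indirect effects. It names no covariates for the mediation models, no assumption about confounding between mediator and BP, and no sensitivity analysis for it.

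Other sections bear on this:

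- Consent, Assessments, and Randomization: "participants will be randomly assigned in a 1:1 ratio to the intervention or active control condition". Only the arm is randomised. Survey and clinical measures are taken at the same three visits.
- Planned Analyses, on covariates: "Discrepancies in baseline values across conditions will inform covariates for inclusion when testing our main hypotheses of interest".
- Antecedent Variables and Qualitative Data: "we will also collect variables hypothesized to be antecedents or important confounders when exploring intervention effects". Table 2 lists them, among them demographics, anthropometry and comorbidities, but no section says how they enter a model.
- Introduction: "Evidence suggests that psychological well-being is related to healthier BP profiles and plays a protective role in disease incidence".
- Strengths and Limitations: "both trial participants and assessors (research staff collecting outcome data) are aware of randomization assignment".

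**The concern.** A mediation claim needs two causal links: arm to mediator, and mediator to BP. Randomisation supports the first link and the total effect of arm on BP. It does not support the second. People with higher well-being may have lower BP for reasons that predate the trial, such as age, body weight, illness or treatment. If so, the mediator coefficient in the BP regression is non-zero without any causal effect. Once the intervention moves the questionnaire score, the product is non-zero too, and its bootstrap interval may exclude zero.

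The Introduction rests on observational associations of this kind, and the curriculum is designed to move the scores. The setting in which the test misleads is therefore close to the one the trial expects. At stake is the mechanistic claim that the intervention lowers BP through well-being. The primary BP comparison is not affected.

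**Working it through.** **1. The plan's own figure.** Planned Analyses gives a difference of 6 mm Hg, SD 12, correlation 0.60, two-sided alpha 0.05, 80% power, one baseline and two follow-up measures. The analysis-of-covariance variance factor is (1 + 0.60)/2 − 0.60² = 0.44. Then n = 2 × (1.960 + 0.842)² × 12² × 0.44 / 6² = 27.6, so 28 per arm. With 20% attrition, 28/0.80 = 35 per arm, or 70 in total. Both stated figures reproduce. They concern the BP comparison; the article gives no figure for the mediation test.

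**2. Model that ignores baseline.** Let a be the shift of the mediator by arm in SD units. Let r be the size of the within-arm mediator-BP correlation, with no causal effect behind it. The documents give neither, so a range is used: a = 0.5 or 0.8, r = 0.2 to 0.4 (negative in sign). The interval excludes zero roughly when both paths are significant.

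- Path a, 28 per arm: Φ(a × √14 − 1.96) = 0.464 for a = 0.5 and 0.849 for a = 0.8.
- Path b, 56 people, arm adjusted for: Φ(atanh(r) × √52 − 1.96) = 0.309, 0.607 and 0.863 for r = 0.2, 0.3 and 0.4.

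The table sets the product of the two against a simulation (600 trials per setting, 1,000 percentile-bootstrap resamples, no effect of mediator on BP).

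| r | a = 0.5: formula / simulated | a = 0.8: formula / simulated |
|---|---|---|
| −0.2 | 14% / 14% | 26% / 25% |
| −0.3 | 28% / 26% | 52% / 53% |
| −0.4 | 40% / 41% | 73% / 72% |

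With r = 0 and a = 0.8 the simulated rate is about 4%, so the excess comes from confounding and not from the bootstrap. The rates are per mediator.

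**3. The arm-imbalance rule, if carried over.** This simulation has one baseline cause shared by mediator and BP, 1,000 trials and 500 resamples. The cause differs between arms at p < 0.05 in only about 5% of trials, as randomisation implies. At 28 per arm, a = 0.5 and r = −0.3, false mediation occurs in 26% of trials with no covariate, 24% with the cause added only when imbalanced, and 2.7% with it always included. Where the arm shifts the mediator, always including it gives 2.7 to 6.4% across settings, at 28 or 35 per arm. Adding a direct effect on BP of 6/12 = 0.5 SD does not remove the problem: the rate under the imbalance rule is then 29%.

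**4. Using baseline, when confounding is stable.** Return to the model of step 2, where 60% of each variable's variance is a stable trait.

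- Adjusting for baseline mediator and baseline BP gives 4.5, 5.0 and 9.3% (a = 0.5) and 7.2, 8.3 and 13.5% (a = 0.8) for r = −0.2, −0.3 and −0.4. At 13.5% of 600 trials the simulation error is 1.96 × √(0.135 × 0.865/600) = 2.7 points.
- Change scores give about 3 to 10%.
- Using the 5-week mediator with 12-week BP on top of baseline adjustment changes little: 4.7, 5.2 and 7.2%, and 5.7, 9.7 and 13.5%.

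**5. Using baseline, when mediator and BP fluctuate together at a visit.** Assume a correlation of −0.3 between the visit-specific parts. In change scores the stable parts cancel and this correlation remains. The SD of a change is √(2 × (1 − 0.60)) = 0.894. Path a is then Φ(0.5/0.894 × √14 − 1.96) = 0.55, or 0.92 for a = 0.8. Path b is 0.607 as before. The products are about 34% and 56%. Simulated rates for change scores and baseline adjustment in this setting run from 31 to 77%.

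**The case against.** The strongest reply is that the high rates describe a model the article does not specify. Aim 2 speaks of improvements, uses group-by-time terms and mentions multiwave models. Planned Analyses frames the outcome as change in BP and cites baseline adjustment for the sample size. If the mediation models use change or baseline, stable confounding largely cancels (step 4). This stands: a reader might take 14 to 72% as the error rate of the planned analysis, but no section says that baseline will be ignored.

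A reader might also infer that the mediation covariates will be chosen by arm imbalance. The article attaches that rule to its main hypotheses. The hypotheses at the end of the Introduction cover BP, well-being, behaviors and inflammation, not mediation. Nor were confounders overlooked: Table 2 plans to collect them. The same-visit schedule does not show that the mediator fails to precede BP in the analysis either, because the remark on time intervals may point to a lagged model.

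Finally, an article may leave path equations to a fuller plan, and the aim is worded as exploring, in a Phase II pilot. This lowers the weight but does not dispose of the point. The article does commit to a test and to a causal question, and exploring whether something is responsible is still a causal reading. Steps 4 and 5 show that change scores or baseline adjustment alone would not secure that reading.

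**Conclusion.** The point holds in a limited form. A bootstrapped product term cannot by itself show that well-being is responsible for better BP, because the mediator-to-BP path is not randomised and the Aim 2 section fixes no adjustment for it. The one covariate-selection rule in the article would not supply that adjustment.

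The size depends on choices the article leaves open and on figures it does not give. With 28 per arm and the assumed shifts and correlations, false mediation is roughly 14 to 72% if baseline is ignored. It is about 3 to 14% with baseline adjustment or change scores and stable confounding. It is 31 to 77% even with those if mediator and BP share visit-level fluctuation at the assumed −0.3. If the intervention does not move the mediator, or no non-causal correlation exists, the rate stays near or below nominal. This is a worthwhile correction to a secondary aim and does not threaten the primary comparison.

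**What to change.** State in Aim 2 that every mediation model will include, in both regressions and whether or not they differ by arm:

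- the baseline value of the mediator and baseline BP;
- a fixed set of Table 2 confounders at their baseline values, for example age, sex, BMI and antihypertensive use. Baseline values matter because later medication use is itself listed among the healthy behaviors that may be tested as mediators.

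Report the result as exploratory, with a sensitivity analysis showing how much residual mediator-outcome confounding would remove the indirect effect. Replace the wording 'are responsible for' with 'are consistent with mediating'.

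The 5-week mediator with 12-week BP can be added as a supporting analysis that sets temporal order. It should not replace the 5-week outcome: it did not reduce the error under stable confounding, and it could miss an effect that has faded by 12 weeks.

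No new data are needed. The cost is a few degrees of freedom and a weaker mechanistic claim.

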#### Aim 3: Evaluate Intervention Effects on High-Sensitivity C-Reactive Protein

Similar analytic techniques as previously described will be used when testing intervention effects on chronic inflammation. Specifically, the term capturing Group×Time interaction will test whether lower levels of inflammation are evident at 8 weeks postbaseline for the intervention group versus the active control arm.

## Results

Activities of the Spanish-language *¡Alégrate!* intervention were funded in 2017, and data collection is ongoing. We expect to submit the trial results to peer-reviewed publications in 2021, soon after recruitment has been concluded and statistical analysis is finalized.

## Discussion

### Principal Findings

This paper describes the design and protocol of the *¡Alégrate!* program, which is a web-based positive psychological intervention tailored for Hispanic/Latino people with hypertension—with the curricular content and evidence-based skills disseminated fully in the Spanish language. Novel interventions specifically geared toward Hispanic/Latino adults are greatly needed, as this racial/ethnic group constitutes the largest minority group in the United States and they experience continued and ever-growing health disparities and high burden of cardiovascular disease risk factors [12,18]. As such, our Spanish-language web-based *¡Alégrate!* program has the potential to positively impact cardiovascular health profiles of Hispanic/Latino adults, particularly when it comes to BP control. Moreover, it offers a more cost-effective alternative to face-to-face delivery of our intervention through dissemination using a web-based platform—accessed through the comfort of an individual’s home.

### Strengths and Limitations

Limitations are evident in the design and eventual deployment of the *¡Alégrate!* web-based trial. Selective enrollment has the potential to introduce bias as Hispanic/Latino people with limited technological proficiency may decline to participate in the trial, or if enrolled, may have difficulty in connecting to Wi-Fi or in navigating the study site. Future trials may want to explore more user-friendly modalities that require little to no coaching that may be more appealing to less technologically savvy community members. We are recruiting in a Chicago-based neighborhood with a large population of Hispanic/Latino adults, the majority of which are of Mexican ancestry. Thus, the findings of the trial may not generalize to the wider, more heterogeneous Hispanic/Latino population across the United States with differences by country of origin, nativity status, and level of acculturation. Our design includes an active control condition where participants are asked to report their emotions, thrice weekly, via our web-based platform. This may not adequately adjust for effects derived from social support and contact with research staff as imparted in the treatment group. Future trials may want to deploy a more active control condition where participants’ access to web-based content is unrelated to the outcome of interest, for example, money management skills. Finally, blinding occurs only at the level of data analysis, and both trial participants and assessors (research staff collecting outcome data) are aware of randomization assignment, which can introduce unintended bias.

Despite these limitations, the strengths of our design are evident. We are the first to design and deliver a Spanish-language positive psychological intervention to Hispanic/Latino adults using a web-based platform. Second, we are collaborating with a Chicago-based clinic located in a neighborhood with residents predominantly of Hispanic/Latino origin, that is, approximately 21,500 Hispanic/Latino people, primarily of Mexican-American descent. Our partnering clinic is also a federally qualified site servicing the most vulnerable, including those with limited income and those with no health insurance. Finally, we provided all enrollees with an investigator-purchased tablet computer and developed detailed Spanish-language user guides (with screenshots) to assist participants in accessing our website, with research staff available via phone for additional tech support.

### Conclusions

Hispanic/Latino people are a vital population for testing our *¡Alégrate!* web-based programs due to an overwhelming need for interventions to improve cardiovascular health and evidence that psychological well-being may be a particularly relevant target. This is especially true within the context of a cultural group that values building of positive emotional bonds and encourages *personalismo* (ie, emphasis on agreeableness, politeness, or courtesy)—and, who despite these positive cultural inclinations, constitutes a collective group that experiences widening cardiac-related health disparities. Our team previously tested our positive psychological curriculum as delivered face-to-face by a psychologist/social worker in a group setting and in the Spanish language [19,42]. We found significant improvement when examining pre-post intervention changes in emotional vitality, subjective happiness, and engagement in happiness-inducing behaviors (eg, meditation). However, rates of retention were particularly low and often involved the inability to attend on-site sessions because of shifts in work schedules, inclement weather, and/or travel outside of the country. Offering an alternative to access our intervention content via a website, from the comfort of home and in a self-paced manner, may prove to be a viable and more effective alternative for Hispanic/Latino adults. This new delivery modality may also prove to be more cost-effective when compared with in-person delivery by a highly trained clinician.

As the use of technology continues to expand, it is imperative that vulnerable populations and ethnic/racial minorities are taken into account during its inception and expansion. How might technology be deployed within a more user-friendly interface for those with limited exposure to technology or those with little formal educational training who experience literacy challenges? For instance, the website for the current *¡Alégrate!* trial was created using inclusive design principles and usability testing to create a simple, straightforward interface to foster high rates of retention and acceptability. The home screen for our tablets was clutter-free with only 1 to 2 apps available that directly linked participants to our study website—with parameters imposed that restricted the addition of new apps and/or the visitation to entertainment sites, for example, Netflix and YouTube. Finally, websites and clinical apps developed from evidenced-based curricular content should be made available in the Spanish language, and other languages for mass and equitable consumption. Tech companies and their employees (eg, software engineers) will need to be creative to ensure that emerging technology is accessible to all—even those with limited technology experience, low literacy, and limited economic resources.

